## Abstract

**Background:**

Patients with asthma often consider their symptomatology a barrier to exercise, leading to a reduced physical activity level. This study aims to determine whether the effect of a Nordic walking (NW) training program plus education and usual care is superior to educational and usual care only, in terms of exercise tolerance and other health-related outcomes in patients with asthma. The second aim is to explore the patients’ experience with the NW program.

**Methods:**

A randomized controlled trial will be conducted with 114 adults with asthma recruited in sanitary area of A Coruña, Spain. Participants will be randomized to NW or control groups in blocks of six and in the same proportion in each group. Participants in the NW group will enrol in supervised sessions during eight weeks, three times/week. All participants will receive three educational sessions on asthma self-management plus usual care (S1 Appendix). Outcomes such as exercise tolerance (primary outcome), physical activity level, asthma-related symptoms and asthma control, dyspnea, lung function, handgrip strength, health related quality of life, quality of sleep, treatment adherence and healthcare resources use will be measured pre and postintervention, and at three and six months of follow-up. Participants in the NW group will additionally participate in focus groups.

**Discussion:**

This is the first study analysing the effect of NW in patients with asthma. NW combined with education and usual care is expected to improve exercise tolerance, but also asthma-related outcomes. If this hypothesis is confirmed, a new community-based therapeutic approach will be available for patients with asthma.

**Trial registration:**

Study registered in ClinicalTrials.gov with number of register NCT05482620.

## Introduction

Asthma is one of the world´s largest non-communicable diseases [1], affecting 339 million people [2]. It is considered a major social and health concern, being associated with a high economic burden, related to days out of work and school, emergency department visits, hospitalizations and mortality [3, 4].

Asthma is characterized by a reversible airway obstruction presented with any combination of the following manifestations and symptoms: wheezing, dyspnea, cough, chest tightness, mucus hypersecretion and airway hyperresponsiveness [5]. Due to these symptoms, patients with asthma, in comparison to their peers, are characterized by lower levels of physical activity [6–10]. They also commonly exercise at lower intensities, mostly because they believe that their disease is a barrier to exercise [9, 11, 12]. In its turn, inactivity can lead to worsening in asthma symptoms and control, health-related quality of life (HRQoL) [13], and a decline in lung function, particularly in forced expiratory volume in one second (FEV_1_), in FEV_1_/forced vital capacity (FVC) ratio, and peak expiratory flow (PEF) [11, 14, 15].

According to the Global Initiative for Asthma (GINA) [16], adults with asthma should engage in physical activity and exercise programs for their overall health benefit. Nevertheless, recommendations on how to perform physical activity or exercise as a part of their treatment is missing in this guideline. There is some evidence showing a positive effect of exercise programs, such as walking, jogging or cycling, reducing exacerbations and rescue medication use [17], and improving asthma-related symptoms, asthma control, lung function [18], exercise tolerance, and HRQoL [19].

Nordic walking (NW) is one of the exercise programs that could have potential benefits for people with asthma. The main difference between NW and conventional walking is the use of two poles to boost the walk, involving for instance the upper limb during the march. It was born in Finland during the 1930s as a cross-country skiers training, and it was been developed, transitioning from skiers to university and educative fields, and then to literature and scientific publications [20, 21]. The evidence is still scarce, but it has shown benefits in exercise tolerance and HRQoL in other chronic conditions, such as metabolic syndrome, musculoskeletal disorders, Parkinson disease [22–24], cardiovascular diseases [25] and chronic obstructive pulmonary disease (COPD) [26]. In COPD, NW improved exercise tolerance (measured as meters walked in six-minute walking test-6MWT); daily physical activity levels; dyspnea; anxiety and HRQoL. COPD and asthma are both respiratory diseases that share common symptoms and signs, such as cough, dyspnea and limited air flow, as well as limited exercise tolerance. Therefore, we hypothesize that similar benefits with NW can also be achieved in patients with asthma.

Thus, the primary aim of this clinical trial is to determine whether the effect of a NW training program plus education and usual care is superior to education and usual care only, in terms of exercise tolerance and other health-related outcomes, in patients with asthma. Secondary, we aim to explore the patients’ experience with the NW program.

## Material and methods

### Study design

This is a two-arm, parallel, randomized controlled trial (RCT) to analyse the effects of an eight-week NW program plus education and usual care compared to education and usual care alone in patients with asthma (NCT05482620). Assessments will take place at baseline, after 8-weeks and then at three and six months of follow-up. This study will be conducted in A Coruña, Spain between June 2022 and June 2024. This protocol is reported according to the Standard Protocol Items: Recommendations for Interventional Trials (SPIRIT) guidelines (S1 Checklist) [27].

### Eligibility criteria

Subjects will be included if they have a clinical diagnosis of asthma, have at least 18 years old, have the desire of take part in the study, and the ability to understand and sign the informed consent. Exclusion criteria include: smokers, diagnosis of other respiratory disease; occurrence of an asthma exacerbation or respiratory tract infection in the last four weeks; acute myocardial infarction in the last six months; cardiac arrhythmia with a IIIb or superior grade in Lown scale; gait disorders due to neuro-muscle-skeletal system problems; comorbidities that implies reduced ability to exercise (e.g., severe anaemia, electrolyte imbalance, hyperthyroidism) [28, 29]. Subjects that are already engaging in exercise sessions of more than 30 minutes per day with a moderate or vigorous intensity; participated in a pulmonary rehabilitation program in the last three months [30], and are pregnant and lactating women will be excluded. In addition, subjects that present contraindications to perform cardiovascular exercise, following the American Heart Association [31] and to perform the 6MWT following the American Thoracic Society / European Respiratory Society (ATS/ERS) [32] criteria, will be excluded too.

### Sample size

To estimate the sample size needed, we used the tool created by the Clinic Epidemiologic and Biostatistics service from A Coruña University Hospital Complex (CHUAC) (http://bitly.ws/sDIp). This calculation was based on the 6MWT minimum clinically important difference in patients with asthma, which is set at 26 meters [33]. Using a standard deviation (SD) of 45.49 meters, obtained from a previous pilot study [34], and considering a power of 80%, an alpha level of 0.05, and a dropout rate of 15%, a total sample size of 114 is estimated (57 in each group).

### Recruitment

Subjects will be screened by physicians during consultations in the pulmonology and allergy services from the pulmonology and allergy services from A Coruña sanitary area and in primary care centres.

Subjects eligible in the study will be listed, and one researcher will be responsible to randomise blocks of six to either the NW group or control group (CG) in the same proportion. Randomization will be performed via a computer program for randomization (http://randomization.com/). The allocation will be made attending to the identification (ID) number, which will be then linked to the participants’ name in the list. The order will be unchangeable, once assigned.

### Blinding (masking)

The assignment to the groups will be made after the baseline evaluation. The physiotherapist in charge of the evaluation will be concealed from which group belongs each subject, and data obtained will be indexed in the database, using study ID numbers only to identify data. Due to the nature of the interventions, the physiotherapist in charge of conducting it, will not be blinded to the allocation.

### Intervention

Participants in both groups will attend three educational sessions together after the baseline assessment (S1 Appendix) (before the NW program starts for the experimental group). Participants will only know the result of the randomization after the education. Educational sessions will be conducted with groups of approximately 6–10 patients. Sessions will be facilitated by a physiotherapist, and will take place in the Faculty of Physiotherapy of The University of A Coruña. Different concepts and guidance related to asthma self-management will be addressed, based on an informative brochure built by the research team. This brochure will be provided to the participants at the end of the education component. If patients miss one session, they will be phone called to wonder about reasons, to be encouraged to assist next sessions and an individual education session will be scheduled to address the missed topic. Besides, patients should keep their usual care, namely attend their regular medical appointments, take the medication under prescription and follow physician recommendations as usual.

Participants in the NW group will additionally enrol in an eight-week NW program [35] of three sessions per week (total of 24 sessions). Feasibility of the NW program has previously been tested in four patients, who showed a good acceptance and satisfaction with intervention received [34]. Each session will last one hour and include: a warm-up period of 15 minutes with articular mobility, body-weight exercises with walking poles, and five minutes of walking without poles; 30 minutes of NW, with an intensity of 70–85% theoretical maximum heart rate (HRmax = 206.9 –(0.7 x age)) [36]; cold-down period of five minutes of relaxed walk without poles, stretching and breathing exercises. NW program will be provided by the same physiotherapist in charge of the educational component, who was trained in NW in Finland. When participants fail one exercise session, he/she will be called to wonder about reasons and to be encouraged to participate in the next session. After finishing the eight-week period, participants will be encouraged to continue by themselves the NW sessions and a pair of poles will be provided to achieve this objective.

### Outcomes

#### Primary outcome

The primary outcome will be exercise tolerance, measured by the distance walked during the 6MWT, a reliable and validated test in patients with asthma [37], which is strongly related with important clinical outcomes as dyspnea and fatigue perceived [32].

#### Secondary outcomes

Exercise tolerance will also be assessed through the number of repetitions during the one-minute sit-to-stand test (1MSTST). This test is focused in lower limb function, especially quadriceps force [38].

The secondary outcome measurements will include physical activity level (accelerometry, International Physical Activity Questionnaire -IPAQ, and patient’s diary), asthma-related symptoms and asthma control (Control of Allergic Rhinitis and Asthma Test -CARAT and patient’s diary), dyspnea (modified Medical Research Council -mMRC, and Borg scale), lung function (spirometry), handgrip strength (hand dynamometry), HRQoL (European Quality of Life Questionnaire– 5 dimensions– 5 levels -EQ-5D-5L, mini Asthma Quality of Life Questionnaire -miniAQLQ), quality of sleep (Pittsburgh Quality of Sleep Index -PQSI), treatment adherence (Test of Adhesion to Inhalers -TAI, and patient’s diary), and healthcare resources use (patient’s diary).

#### Other measures

Respiratory muscle strength (maximum inspiratory -MIP and expiratory pressure -MEP) will be assessed to characterize sample, since no change with NW program is expected. Correlation with other outcomes such as exercise tolerance and physical activity will be explored [39].

Adverse effects reported by the participants will be registered.

Qualitative data will be collected through focus groups to a better understanding of participants’ experience with NW, namely: experience and satisfaction with the intervention received, facilitators and barriers to their participation perceived improvement in asthma management and the way of afront their disease.

### Data collection methods

All the assessments will take place at the Faculty of Physiotherapy in The University of A Coruña. Assessments will be performed by the same trained physiotherapist (different from the one in charge of interventions), blinded to the group allocation. The evaluator has been trained to perform these assessments, in which she also has previous experience. To avoid the risk that participants reveal to which group they belong during the first evaluation, the allocation will be only made after all baseline measurements and the education component. The evaluator will be also blinded during the following assessment visits. In the case this blinding is compromised due to the possible comments of the participants, this will be reported. When a participant fails an evaluation appointment, the evaluator will contact him/her in order to propose a date to a new appointment.

After reading the information sheet and signing the informed consent, an anamnesis will be performed in order to collect the sociodemographic variables (age, sex, occupation…), past history (e.g., surgical, comorbidities, etc.) and to confirm the fulfilment of the eligibility criteria.

All questionnaires, excepting IPAQ, will be self-completed by the participants after a brief explanation of the evaluator. The evaluator will be available to clarify any doubts during the questionnaires filling and at the end will check if all questions were covered.

All outcomes will be measured at baseline, postintervention, and at three and six months follow-up, except respiratory muscle strength (measured only at baseline) and treatment adherence and healthcare resources use (not analysed at baseline). Adverse effects related to following described outcomes, or during intervention, will be registered if pertinent.

Exercise tolerance will be measured with 6MWT and 1MSTS. To perform the 6MWT, an indoor corridor 30 metres long will be used, following ATS/ERS guidelines [32]. Before and after the test, vital signs (heart rate, oxygen saturation and blood pressure), fatigue of the lower limbs and dyspnea (using the modified Borg scale 1–10) will be recorded [40]. Two tests will be performed, with a minimum rest of 30 minutes, and the longest distance of the two tests will be selected for the analysis. For the 1MSTST, an armless chair will be used to ensure the upper limbs are not taking part in action. Subjects will be instructed to perform as many sit-to-stand movements that they can do in one minute [41, 42].

Accelerometry and the IPAQ, short form will be used to assess physical activity. The accelerometer MoveMonitor DynaPort®MM+ (McRoberts, The Hague, the Netherlands) will be used to register physical activity during seven days. Time lying down, sitting, standing up and walking, number of steps per day, intensity of movement, kilocalories consumed and metabolic equivalent of task (MET), will be analysed. Validity of accelerometer has been documented in COPD [43] and this tool has been used in previous studies in patients with asthma [44]. Besides, we will use IPAQ-short form, administrated through personal interview. The questionnaire has been validated in the Spanish population [45] and results will be analysed following the indications of the IPAQ group [46]. Also, number of steps per day should be recorded by patients in their patient’s diary, registered by a Google Fit ® Smartphone App (Google LLC, Mountain View, CA, USA); and register of their physical activity or exercise performed on the non-session’s day and once the sessions period has finished.

Asthma-related symptoms and asthma control will be measured using the CARAT, validated in patients with asthma [47], which has been used in Spanish population [48]. Additional analysis will be made from data extracted from the patient´s diary, in terms of dyspnea measured with modified Borg scale, expectoration, cough, perception of wheezing, work absence due to asthma symptoms or avoidance of doing some activity due to same reason. Related to dyspnea, it will be assessed also during personal interview using the mMRC scale [49]. In addition, modified Borg scale will be used before and after each NW session [40].

Lung function will be assessed with a spirometry following international recommendations of ATS/ERS [50]. FEV_1_, FVC, FEV_1_/FVC, forced expiratory flow at 25 and 75% of the pulmonary volume (FEF_25-75%_) and PEF will be recorded, obtained with a spirometer (Datospir® 120C, Sibelmed, Barcelona, Spain). Moreover, PEF will be assessed every day by patients in their diary. A peak-flow meter will be provided to each patient by the study.

Handgrip strength will be measured in both hands, registering data in kilograms, and using Jamar® hand-dynamometer (Performance Health, Warrenville, IL, USA) and following Mathiowetz et al. protocol [51].

HRQoL will be assessed using a generic and asthma-specific questionnaires. EQ-5D-5L has been validated in patients with asthma [52] and in Spanish population [53]. MiniAQLQ has been validated to use in this population [54], and has already been used in Spanish context [55, 56].

Quality of sleep will be assessed using PQSI, validated in Spanish [57].

Related to treatment adherence, inhaler adherence will be evaluated using the TAI, validated in patients with asthma and in the Spanish population [58]. Also, participants should note in their diary when, what and in which dosage need take medicine in order to relieve symptoms.

Healthcare resources use will be analysed as well taking in count data from patient’s diary (emergency service or unscheduled medical visits due to asthmatic symptoms).

Respiratory muscle strength will be measured by MIP and MEP, following Spanish Society of Pneumology and Thoracic Surgery (SEPAR) recommendations [59]. A digital manometer MicroRPM® (Vyaire Medical GmbH, Hoechberg, Germany), a flanged mouthpiece and the PUMA® software (Vyaire Medical GmbH, Hoechberg, Germany) will be used. At least six acceptable measurements are required and three of them should be reproductible, with less than 5% of difference between them.

Qualitative data will be obtained through focus group meetings, moderated by an experienced researcher. Another researcher will take part in the meeting to observe and take notes. These two researchers, will start introducing themselves and then moderator will give a clear explanation of the aim of the meeting before starting. Then, following a semi-structured guide with open-ended questions (S2 Appendix), focus groups will be conducted in order to gather a better understanding of participants experience. Around 15 participants will participate in focus groups [60], after receiving the NW program. Every NW group will constitute a focus group. Focus groups will be conducted in a room of the Faculty of Physiotherapy, in the University of A Coruña, and are expected to last about 90 minutes. Focus groups will be recorded (video and audio) and transcribed under consent of participants.

Participants dropping out of the study, if any, will be contacted to record possible reasons, and in case they are from the NW group they will also asked regarding the possibility to participate in the focus group and to provide data registered in their diary.

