### Statistical analysis

Quantitative data will be expressed as mean and SD when normally distributed and as median and quartiles (Q1-Q3) when not normally distributed. Normality will be explored with Kolmogorov-Smirnov tests. To compare outcomes between NW group and CG, ANOVA tests for repeated measures or Kruskal-Wallis tests will be used, as appropriate in function of normality of data distribution. All this data will be analysed using SPSS (IBM Corp., Armonk, NY, USA) program, version 26.00.

To analyse qualitative data, two of the researchers, following Braun et al. [61] recommendations, will deep read all transcripts and will make notes through text, to generate initial codes independently from each other. Then, the text will be re-read, searching and reviewing themes in relation to these codes, to be able to define and name the themes. After that, report can be produced. Another member of the team will check data to ensure credibility and trustworthy of findings, and through peer debriefing technique [62], researchers can be aware of their interpretation with the possibility to clean them of preconceptions or wrong assumptions. Agreement will be measured through agreement percentages, calculated as the number of thematic units in which evaluators agree divided by total number of units. Also kappa of Cohen will be used, considering >0.81 almost a perfect agreement [63].

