## Results and discussion

This RCT aims to assess effectiveness of NW in patients with asthma. The study has been prospectively registered, and to our knowledge, it is the first study exploring this topic. Nordic walking is still a recent and novel exercise training modality, with few studies published in the health field. Based on previous studies about exercise programs [17–19], we hypothesise that the NW program in patients with asthma will increase exercise tolerance, physical activity level, asthma-related symptoms, asthma control, and HRQoL. Due to the characteristics of the intervention (involvement of the upper limbs), handgrip strength could also get improved [64]. We are expecting that lung function remains unchanged [65, 66], but as there is some controversy in current literature, we have decided to collect this data at all time-points [18, 19]. If the beneficial effects of NW are demonstrated, a new community-based therapeutic approach can be added to the current recommended and implemented in clinical practice. Nordic walking is affordable and feasible in the community, taking advantage of blue and green spaces in every patient´s environment–following Urban Training® concept–that have already shown benefits in terms of physical activity in patients with COPD [67]. Indirectly, the demonstration of our hypothesis could lead to added benefits, if the use of rescue medication, or medical visits (emergency department or unscheduled visits) are reduced: deriving from that reduction in healthcare resources use, a mitigation in socio-sanitary costs could be achieved.

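### The abstract and the methods disagree on whether treatment adherence and healthcare use have a baseline value; reconcile them, and preferably give the TAI at T0.

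*Protocol article*

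**What the plan says.** The Methods paragraph of the abstract gives one schedule for a list of outcomes, and the list ends with the two at issue: "treatment adherence and healthcare resources use will be measured pre and postintervention, and at three and six months of follow-up".

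Data collection methods sets a general rule of four time points (baseline, post-intervention, three and six months) and then names exceptions. Respiratory muscle strength is taken at baseline only. The other exception is "treatment adherence and healthcare resources use (not analysed at baseline". No reason is given for it.

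Secondary outcomes names the instruments: "treatment adherence (Test of Adhesion to Inhalers -TAI, and patient’s diary), and healthcare resources use (patient’s diary". Healthcare use is drawn from the "patient’s diary (emergency service or unscheduled medical visits due to asthmatic symptoms".

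Study design states "This is a two-arm, parallel, randomized controlled trial (RCT", and Statistical analysis states "To compare outcomes between NW group and CG, ANOVA tests for repeated measures or Kruskal-Wallis tests will be used". That section makes no separate provision for outcomes without a T0 value. Results and discussion mentions, as a possible indirect benefit, what would follow "if the use of rescue medication, or medical visits (emergency department or unscheduled visits) are reduced".

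**The concern.** A reader of the abstract expects pre and post values of adherence and healthcare use. A reader of the methods expects post-intervention values only. The difference determines what the evaluator collects at T0 and which analysis is possible afterwards.

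If the methods text governs, three things are given up for these outcomes: change within a patient, a look at whether the arms started alike, and adjustment for the starting level. The common analysis rule also fits them less well, because a repeated-measures model would begin at T1, after the programme has ended.

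For the TAI the exemption looks avoidable. Data collection methods says that all questionnaires except the IPAQ are self-completed, with the evaluator available to help, so the TAI could be given at T0 with the others.

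**Working it through.** **1. The two schedules side by side**

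| Outcome | Abstract | Data collection methods |
|---|---|---|
| Treatment adherence (TAI, diary) | T0, T1, T2, T3 | T1, T2, T3 |
| Healthcare use (diary) | T0, T1, T2, T3 | T1, T2, T3 |

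The methods text says not analysed, where it might have said not measured. It stands, however, as an exception to a rule about what is measured, so absence at baseline is the natural reading. If the values are in fact collected and only left out of the analysis, that too needs saying.

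**2. The plan's own figure.** The Sample size section uses 26 m, SD 45.49 m, 80% power, alpha 0.05 and 15% dropout, all for the 6MWT. Per arm, two-sided: 2 × (45.49 × (1.960 + 0.842) / 26)² = 48.05. Dividing by 0.85 gives 56.5, hence 57 per arm and 114 in total. The figure reproduces and does not depend on this point. The plan states no figure for adherence or healthcare use.

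**3. What the repeated-measures ANOVA would test.** Suppose the NW arm differs from control by a constant d at T1, T2 and T3, and by 0 at T0.

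- With T0 in the model, the differences are 0, d, d, d. They change over time, so the benefit shows in the group-by-time term. The group main effect averages (0 + d + d + d)/4 = 0.75d.
- Without T0, the differences are d, d, d. The group-by-time term is 0 and the whole benefit is in the group main effect.

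The term that carries the answer is therefore not the same for these two outcomes as for those measured at T0. The Kruskal-Wallis alternative, applied at a follow-up visit, needs no baseline.

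**4. Precision, under an assumed correlation.** The documents give no baseline to follow-up correlation r, so a range is shown. With linear adjustment of a roughly continuous score, residual variance is multiplied by 1 − r², a cut of r². With 48 evaluable per arm (57 × 0.85 = 48.45), the standardized difference detectable with 80% power is (1.960 + 0.842) × √(2v/48). Here v = 1 for follow-up only, 1 − r² for baseline as covariate, and 2(1 − r) for change from baseline.

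| r | Variance cut from adjustment | Follow-up only | Baseline as covariate | Change from baseline |
|---|---|---|---|---|
| 0.3 | 9% | 0.57 SD | 0.55 SD | 0.68 SD |
| 0.5 | 25% | 0.57 SD | 0.50 SD | 0.57 SD |
| 0.7 | 49% | 0.57 SD | 0.41 SD | 0.44 SD |

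The gain comes from using baseline as a covariate. A change score gains nothing at r = 0.5 and loses precision at r = 0.3.

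**The case against.** The strongest reply is that a randomized trial with a concurrent control needs no baseline value. A reader might infer that, without one, the trial cannot show fewer visits or less rescue medication. The documents do not support that. A lower follow-up level in the NW arm than in the control arm is valid evidence of a reduction due to the programme, and the discussion speaks of reductions only conditionally, without promising a within-patient change. This part of the reply stands in full.

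A reader might also infer bias because the earliest value is taken after self-management education. The Intervention section has both arms attend the same sessions together before they learn their allocation, so the contrast between arms is not biased.

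Nor should the variance cuts be read as a fixed loss for both outcomes. They rest on an assumed r and on linear adjustment of a continuous score. Diary counts of emergency or unscheduled visits fit that poorly, and Statistical analysis as written plans no covariate adjustment. Chance imbalance in an unmeasured covariate is already covered by the type I error rate.

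The exemption is also partly coherent. A diary kept during the study cannot supply a pre-enrolment value, so only the TAI can be repeated like for like at T0. CARAT, miniAQLQ and spirometry at T0 already show balance on related features.

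None of this removes the contradiction, the mismatch with the repeated-measures model, or the case for a T0 TAI.

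**Conclusion.** The contradiction between the abstract and Data collection methods is real and must be reconciled. The follow-up comparison between arms remains valid without a baseline, and the primary 6MWT analysis and the sample size are untouched.

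The loss is limited to two secondary outcomes: no within-patient change, no direct balance check, no baseline adjustment, and a repeated-measures analysis in which a constant benefit appears only in the group effect. For the TAI, treated as roughly continuous, the forgone variance cut runs from about 9% to 49% for r between 0.3 and 0.7. For visit counts no such figure is offered. The point is a cheap and specific improvement to the plan.

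**What to change.** - Give the TAI at T0, before the education sessions, and use it as a covariate in the T1 to T3 comparison of adherence.
- Optionally, add to the T0 anamnesis a recall item with a fixed window for unscheduled or emergency asthma visits, as a descriptor and covariate. It is weaker than the TAI because the follow-up data come from a diary. A short window would also say little, since Eligibility criteria excludes an exacerbation in the last four weeks.
- Where no baseline will exist, including healthcare use if no recall item is added, correct the abstract. State that the outcome is compared between groups at follow-up only, and that the group effect is the term of interest.
- Make Data collection methods and the abstract agree with whichever schedule is chosen.

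The cost is a few minutes per participant. Participants already enrolled will lack the T0 value, and the report should say so.
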